## Abstract

**Background:**

Mobile health interventions provide significant strategies for improving access to health services, offering a potential solution to reduce the mental health treatment gap. Economic evaluation of this intervention is needed to help inform local mental health policy and program development.

**Objective:**

This paper presents the protocol for an economic evaluation conducted alongside 2 randomized controlled trials (RCTs) to evaluate the cost-effectiveness of a psychological intervention delivered through a technological platform (CONEMO) to treat depressive symptoms in people with diabetes, hypertension, or both.

**Methods:**

The economic evaluation uses a within-trial analysis to evaluate the incremental costs and health outcomes of CONEMO plus enhanced usual care in comparison with enhanced usual care from public health care system and societal perspectives. Participants are patients of the public health care services for hypertension, diabetes, or both conditions in São Paulo, Brazil (n=880) and Lima, Peru (n=432). Clinical effectiveness will be measured by reduction in depressive symptoms and gains in health-related quality of life. We will conduct cost-effectiveness and cost-utility analyses, providing estimates of the cost per at least 50% reduction in 9-item Patient Health Questionnaire scores, and cost per quality-adjusted life year gained. The measurement of clinical effectiveness and resource use will take place over baseline, 3-month follow-up, and 6-month follow-up in the intervention and control groups. We will use a mixed costing methodology (ie, a combination of top–down and bottom–up approaches) considering 4 cost categories: intervention (CONEMO related) costs, health care costs, patient and family costs, and productivity costs. We will collect unit costs from the RCTs and national administrative databases. The multinational economic evaluations will be fully split analyses with a multicountry costing approach. We will calculate incremental cost-effectiveness ratios and present 95% CIs from nonparametric bootstrapping (1000 replicates). We will perform deterministic and probabilistic sensitivity analyses. Finally, we will present cost-effectiveness acceptability curves to compare a range of possible cost-effectiveness thresholds.

**Results:**

The economic evaluation project had its project charter in June 2018 and is expected to be completed in September 2021. The final results will be available in the second half of 2021.

**Conclusions:**

We expect to assess whether CONEMO plus enhanced usual care is a cost-effective strategy to improve depressive symptoms in this population compared with enhanced usual care. This study will contribute to the evidence base for health managers and policy makers in allocating additional resources for mental health initiatives. It also will provide a basis for further research on how this emerging technology and enhanced usual care can improve mental health and well-being in low- and middle-income countries.

**Trial Registration:**

ClinicalTrials.gov NCT12345678 (Brazil) and NCT03026426 (Peru); https://clinicaltrials.gov/ct2/show/NCT02846662 and https://clinicaltrials.gov/ct2/show/NCT03026426

**International Registered Report Identifier (IRRID):**

DERR1-10.2196/26164

## Introduction

Globally, depression affects more than 264 million people each year, with a high prevalence in Brazil and Peru (5.8% and 4.8%, respectively). In Brazil, depressive disorders are ranked as the fourth leading cause of years lived with disability, and thirteenth for causing disability-adjusted life years [1]. In Peru, depressive disorders account for 37% of the years lived with disability attributed to mental health conditions and are responsible for almost 46,000 disability-adjusted life years [2].

Chronic diseases such as hypertension and diabetes can be exacerbated by depression, which is often undiagnosed and thus remains untreated [3,4]. This can lead reduced quality of life, increased physical health complications, and eventually a rise in treatment costs for both the individual and the health economy [4].

In low- and middle-income countries (LMICs) access to mental health care remains extremely limited and unequal, with those living in low-resource areas facing greater difficulties in accessing mental health care [5,6]. This is due to limited resource availability and a lack of trained health personnel. For instance, in Brazil there are only 4.48 specialists per 100,000 inhabitants. A similar scenario is observed in Peru, with 2.06 psychiatrists and 6 psychiatric nurses per 100,000 people [7]. Most Brazilians and Peruvians with clinically relevant levels of depressive symptoms currently do not receive any treatment. There is thus a clear need to address the mental health treatment gap within these settings.

Mobile health (mHealth) interventions offer potentially scalable and affordable solutions to reduce the treatment gap in mental health care (eg, depression). Studies on the effectiveness of mHealth intervention in this regard have shown promising results [8-11].

The Latin America Treatment and Innovation Network in Mental Health (LATIN-MH), 1 of 5 hubs funded by the National Institute of Mental Health (NIMH), conducted 2 randomized controlled trials (RCTs) evaluating the effectiveness of a low-intensity behavioral activation intervention for depression (CONEMO). These aimed to reduce symptoms of depression among individuals with hypertension, diabetes, or both conditions attending public health care facilities in São Paulo, Brazil, and Lima, Peru [12].

The acronym CONEMO is derived from the terms “Control” and “Emotional” (meaning: emotional control). The intervention is delivered via a smartphone app, and minimally supported by a nurse/nurse assistant (NA). The app consists of 18 brief mini-sessions, delivered automatically over a 6-week period, with 3 mini-sessions per week. Each session requires less than 10 minutes to complete [12]. The CONEMO intervention seeks to expand access to mental health care while using the available health services in Brazil and Peru [13].

Although efforts have been made to ensure the effectiveness, feasibility, and affordability of similar interventions, the success and impact are primarily determined by regional differences in cost structures and the burden of chronic diseases [14]. Cost data provide essential information for financial planning and enable decisions to be made regarding implementation feasibility. This cost analysis may provide a critical contribution to the planning and prioritization of interventions to address the large and growing burden of depression in LMICs.

Although there is an increase in economic evaluations of mHealth interventions, evaluations of these interventions in LMICs remain limited [15]. This paper describes a protocol for an economic evaluation to be conducted as part of 2 RCTs evaluating the cost-effectiveness of CONEMO, an mHealth intervention to treat symptoms of depression in people with diabetes or hypertension or both in Brazil and Peru.

## Methods

### Study Design

The economic evaluation will follow the Methodological Guidelines for Economic Evaluation Studies of Health Technologies [16] and will be reported according to the Consolidated Health Economic Evaluation Reporting Standards (CHEERS) checklist [17]. The multinational economic evaluations will be fully split analyses (incorporating estimates of both resource use and clinical effectiveness from the same group of patients from individual countries) with a multicountry costing approach (applying unit cost estimates from individual countries to account for resource use in each of those countries) [18]. The within-trial analyses will be conducted using data from the randomized control trials NCT02846662 and NCT03026426, and secondary data on health service costs extracted from governmental public databases. This protocol outlines the methods for a cost-effectiveness analysis and cost-utility analysis alongside the RCTs conducted in Brazil and Peru, respectively.

The proposed economic evaluations will be conducted from both the public health care system perspective (including only health care system costs) and the societal perspective (including health care system costs plus patient and productivity costs).

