### Estimating Resources and Costs

The cost estimation will involve 3 stages: (1) identification of the costing items used to provide a particular service, (2) measurement of the resources used, (3) application of monetary value for each cost item, and calculation of the unit cost of a particular service [24].

The measurement of the resources will take place over 3 periods, baseline, 3-month follow-up, and 6-month follow-up, in the intervention and control groups. These are the same periods used to assess clinical effectiveness in the RCTs.

The measurement of resource use will be based on the group of patients from each country. The costing approach will apply unit cost estimates from Brazil and Peru to account for resource use in each of those countries.

Costs will be applied to the resources based on the unit costs or price weights most recently published in the respective official government databases (Department of Informatics of the National Health System, Departamento de Informática do Sistema Único de Saúde [DATASUS] in Brazil; and the Integral Health Insurance/Seguro Integral de Salud [SIS] in Peru). Other resource use not recorded in DATASUS or SIS will be based on LATIN-MH databases. These costs will be obtained in Brazilian reals (R$) and Peruvian sols (S$), as per rates in 2017. All costs will be adjusted for inflation using the Brazilian and Peruvian consumer price indexes for the current reference year (2021) and will be converted into international dollars (INT$) using the 2021 purchasing power parity (PPP) conversion factors for Brazil and Peru.

We will use a mixed costing methodology (ie, a combination of top–down and bottom–up approaches) considering 4 cost categories: intervention (CONEMO related) costs, health care costs, patient and family costs, and productivity costs. Table 2 presents an overview of resource use and cost measures that will be used in the economic evaluations. These include costs hypothesized to differ between CONEMO plus enhanced usual care (the intervention group) and enhanced usual care (the control group).

**Table 2 table2:** Summary of cost categories measured.

Cost category and unit					Unit cost		Source of data	

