### Intervention Costs

Intervention costs include the value of the staff time and transport involved in either supervision or training of the primary care workers that will use CONEMO.

We will assume that the intervention (CONEMO) is operational, and so start-up costs, such as design and development of CONEMO, will be excluded. Therefore, we will include only costs for maintenance of the dashboard and app, internet package costs, and expenditures related to office supplies and infrastructure.

All of the research-related costs associated with trial administration, data collection, and outcome assessment of RCTs will be excluded.

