### Health Care Costs

Health care costs will include direct medical costs: outpatient visits, emergency room and hospital admissions, and medicines prescribed during the study period.

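### The Intervention Costs section counts supervision, training and transport, then limits itself to a list without them, and the perspective definitions never name the intervention category

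*Protocol article*

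**What the plan says.** Four places in the protocol article bear on which costs enter the numerator of the incremental cost-effectiveness ratio (ICER).

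- **Intervention Costs.** The section begins: "Intervention costs include the value of the staff time and transport involved in either supervision or training of the primary care workers". It then assumes that CONEMO is already operational, rules out the cost of designing and building it, and continues: "Therefore, we will include only costs for maintenance of the dashboard and app, internet package costs, and expenditures related to office supplies and infrastructure".
- **Estimating Resources and Costs, with Table 2.** The plan works with separate groups of cost, "considering 4 cost categories: intervention (CONEMO related) costs, health care costs, patient and family costs, and productivity costs". It adds that "Table 2 presents an overview of resource use and cost measures that will be used in the economic evaluations". The intervention block of Table 2 has seven rows, including one each for supervision staff, training staff and transport.
- **Health Care Costs.** This category holds clinical use only: "Health care costs will include direct medical costs: outpatient visits, emergency room and hospital admissions, and medicines prescribed during the study period".
- **Study Design.** Two perspectives are defined: "public health care system perspective (including only health care system costs) and the societal perspective (including health care system costs plus patient and productivity costs"). The term for system costs is not defined, and the intervention category is not mentioned in either.

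**The concern.** Within one short section, two statements give different contents for the same cost category. The opening sentence includes staff time and transport for supervision and training. The later sentence, closed by *only*, lists four other items. An analyst who takes the later sentence as the operative rule would leave out costs that the opening sentence and Table 2 both include.

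The Analytic Methods section defines the ICER numerator as the difference in mean cost between the arms. CONEMO's delivery cost differs between arms by design, because enhanced usual care as described has no app, no nurse supervision for it and no training in it. Any part of that cost that is dropped lowers the incremental cost directly, and the error always favours CONEMO.

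The perspective definitions do not settle the matter. They are the place where a reader would look for which categories are counted, and the one category that belongs to a single arm is not named there.

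**Working it through.** The article gives no unit costs or resource quantities, so there is no figure to reproduce. The check compares the text with Table 2 and then follows the consequence through the ICER formula.

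**Step 1. Intervention rows in Table 2 against the two statements in Intervention Costs.**

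| Table 2 intervention row | In the opening sentence | In the *only* sentence |
|---|---|---|
| Supervision staff | yes | no |
| Training staff | yes | no |
| Transport | yes | no |
| Dashboard and app upkeep | not mentioned | yes |
| Internet package | not mentioned | yes |
| Office supplies | not mentioned | yes |
| Infrastructure | not mentioned | yes |

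The *only* sentence keeps 4 of 7 rows and omits 7 − 4 = 3. The omitted rows are exactly the ones that the opening sentence includes. The two statements together make up the full Table 2 list; the second taken alone does not.

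**Step 2. Consequence for the ICER.** Per participant in the CONEMO arm, let K be the mean cost of the four kept rows and S the mean cost of the three omitted rows. Both are zero in the control arm. Let H be the between-arm difference in the other categories counted under a given perspective, and E the difference in effect.

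- Full Table 2 list: ICER = (K + S + H) / E
- *Only* list: ICER = (K + H) / E
- Difference: S / E

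S is positive if any of the three resources was used. The section CONEMO Plus Enhanced Usual Care says that the nurses and nurse assistants were trained and supervised weekly, so S is above zero. With E positive, the ICER under the *only* list is too low by S / E. This applies to 2 countries × 2 perspectives × 2 outcomes = 8 ratios at each time horizon, provided that intervention costs enter both perspectives. S cannot be evaluated from the article.

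**Step 3. Categories against perspectives.**

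| Cost category | Public system perspective | Societal perspective |
|---|---|---|
| Intervention (CONEMO) | not named | not named |
| Health care | within system costs | within system costs |
| Patient and family | not included | named, as patient costs |
| Productivity | not included | named |

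Three categories have a recognisable place. If system costs means all costs that the public system bears, the intervention category falls there, and 7 rows are counted (Table 2) or 4 (the *only* sentence). If the term meant just the category called health care costs, no intervention row would be counted under either perspective. The second reading needs two different terms to be treated as one. It also clashes with the statement that the Table 2 measures will be used in the evaluations.

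**The case against.** **On the *only* sentence.** It starts with *Therefore* and follows directly on the exclusion of development cost. In context it may simply separate the cost of running the platform from the cost of building it. The section's own opening and Table 2 both point to including staff and transport. This is a fair account of the probable intent, and it stands as such. It does not remove the conflict. Weekly supervision is a running cost and is still absent from the list, and training of workers could be taken for a start-up item. The sentence as written decides both the wrong way for anyone who follows it.

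**On the perspectives.** A reader might infer that the plan leaves CONEMO's own cost out of both perspectives, so that the intervention would look almost free. The documents do not support that. Study Design speaks of health care *system* costs, a term about who pays, and not of the category health care costs. The Abstract and the costing section list intervention costs among those considered, Table 2 gives them seven rows, and the Results section says that the costs of CONEMO will be reported. No sentence excludes the category. On the ordinary reading, intervention and health care costs together form the system's costs, and the societal perspective adds the other two categories. What remains is a missing label.

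**On detail left elsewhere.** An article need not assign each cost row to each perspective, and a fuller health economics plan may do so. That answers silence. It does not answer a restrictive rule that the article itself states and that contradicts its own section and table.

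**Conclusion.** The conflict in Intervention Costs is real. Taken literally, the *only* sentence removes 3 of the 7 intervention rows in Table 2 and understates CONEMO's incremental cost in every ICER, in CONEMO's favour. The direction rests on two points that the article supports: these resources were used in the CONEMO arm, and enhanced usual care has none of them. That a lower ratio looks better for CONEMO also assumes a positive difference in effect. The size is unknown, and no figure should be attached to it without unit costs.

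The perspective definitions are a lesser matter. They add ambiguity because they do not name a category that the plan keeps separate, but the natural reading includes it. The point should be corrected as a costing rule that contradicts its own section and table, and not reported as a plan to ignore CONEMO's cost.

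**What to change.** Two changes of wording.

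1. **Intervention Costs:** replace the *only* sentence with the complete Table 2 list: supervision staff, training staff, transport, dashboard and app upkeep, internet package, office supplies and infrastructure. Say that design and development are excluded.
2. **Study Design:** define the perspectives by category. Public health care system perspective = intervention costs + health care costs. Societal perspective = these two + patient and family costs + productivity costs.

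Neither change needs new data, since Table 2 already gives a source for each of the seven rows. The only cost is that the ICERs may look less favourable to CONEMO than under the shorter list. The wording should be settled before the cost comparison by arm is seen.

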### Study Population

All participants in the RCT will be included in the economic evaluations. Participants include patients of the public health care system in Brazil or Peru. Inclusion criteria were adults (age ≥21 years), able to read the screen of a smartphone, receiving treatment for hypertension, diabetes, or both (self-report validated with clinical records), and experiencing symptoms of depression. Symptoms of depression were defined as obtaining a score of 10 or more on the 9-item Patient Health Questionnaire (PHQ-9) [19]. Participants were recruited from 20 primary care units in São Paulo, Brazil, and from 4 primary care centers and 3 outpatient clinics in Lima, Peru.

### Setting and Location

The Brazilian health care system is made up of 2 subsectors: the National Health System (Sistema Único de Saúde [SUS]), which is universal and free for everyone, and private health insurance, which covers approximately 25% of the population. Peru has a decentralized health care system administered by 5 providers: the Ministry of Health (MINSA), which provides health services for 60% of the population; Social Security (EsSalud), which covers 30% of the population; and the Armed Forces (Fuerzas Armadas Españolas [FFAA]), Policía Nacional del Perú (PNP), and private sector, which together provide services to the remaining 10% of the population.

Both Brazilian and Peruvian health care systems have been implementing several reforms over the last 2 decades. As a result, health service networks in these countries are segmented into primary, secondary, and tertiary care levels [6,20]. Patients with diabetes and hypertension are typically seen within primary care in Brazil (primary care units) and within either primary (primary care centers) or secondary care units (hospital outpatient clinics) in Peru.

The trials have been conducted in primary care settings (20 public primary care centers of the SUS) in Sao Paulo, Brazil, and in 4 primary care centers in EsSalud and 3 outpatient clinics in MINSA in Lima, Peru [21].

### Comparators

In the Brazilian and Peruvian health care systems, there is no screening policy for mental health in primary care units, where the focus is on physical health. Mental health care is available within specialized primary and secondary care services in both countries. The usual care in the primary care setting integrates practices of health promotion and clinical practice, which do not include the use of depression screening instruments.

The economic evaluations will compare CONEMO plus enhanced usual care with only enhanced usual care.

### CONEMO Plus Enhanced Usual Care

The intervention group received CONEMO plus enhanced usual care. CONEMO is a low-intensity mHealth intervention aimed at reducing symptoms of depression. It is delivered via a smartphone app, and is minimally supported by a nurse/NA. The CONEMO app delivers 18 brief, automated mini-sessions over a 6-week period, with 3 mini-sessions per week. Each session is completed in less than 10 minutes.

The app content is based on behavioral activation, an evidence-based psychological approach to treat depression. Processed data on app usage were collected automatically and reviewed in real-time by nurses/NAs through a dashboard installed on tablets.

Nurses/NAs met with participants for an initial face-to-face meeting, where participants received a smartphone with the app preinstalled and completed a tutorial on its use. Nurses/NAs made 2 mandatory phone calls to all CONEMO participants at the beginning of the program to troubleshoot any difficulties and enhance motivation for the use of CONEMO. Additional calls were prompted through notifications sent to nurses/NAs when the CONEMO automated system detected nonadherence. Patients could request technical help through the help button on the app. Nurses/NAs received training and were supervised weekly by psychologists through face-to-face meetings or via telephone.

